1. **Protocol Title:** Directly administered vs. self-administered antiretroviral therapy in methadone clinics
2. **Protocol Version and Date of Version:** Version 2.5; June 17, 2010
3. **Study Summary**

We propose to conduct a randomized, unblinded, clinical trial of a medication adherence intervention in opioid-dependent, HIV-infected participants who are initiating new antiretroviral therapy, and who receive opioid agonist maintenance therapy with methadone or buprenorphine at opioid treatment programs (OTPs) in Baltimore, MD. Randomization will be stratified by study site and prior antiretroviral exposure. Two hundred participants will be randomly assigned 1:1 self-administered antiretroviral therapy (SAT) or directly administered antiretroviral therapy (DAART). Subjects assigned to DAART will take morning doses of antiretroviral therapy with a nurse or medical assistant in a private room at the OTP. DAART subjects will be transferred to self-administered therapy after 12 months. This is a 5 year study and participants will be enrolled between month 6 and month 42 of the study. The maximum follow-up for individual participants will be 18 months. Based on our pilot experience we anticipate 50% of subjects will be women, 80% African American, with a median age of 44 years. The following outcomes will be compared in the two study arms:

A. Suppression of the viral load (primary outcome),

B. Changes in CD4+ cell counts,

C. The development of antiretroviral drug resistance,

D. Retention to opioid agonist maintenance therapy, urine toxicology screens for drugs of abuse, and self-reported drug and alcohol use,

E. Self-reported adherence with therapy, retention to ART, and clinical and psychosocial moderators of adherence,

D. Electronically monitored medication adherence, using MEMS caps, in the first 2 months of the study

Outcomes data will be obtained at study assessment visits at baseline, 3 months, 6 months, 12 months, and 18 months. Participants will provide contact information, take an interviewer-administered survey, and provide blood and urine samples at study assessment visits. MEMS cap data will be captured at 1 month and 2 months. Subjects will be compensated for successful completion of study assessment visits and MEMS interrogations.

1. **Study Procedures**
2. Study design, including the sequence and timing of study procedures. Distinguish procedures that are experimental from those which are part of routine care.

Study Design

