Participants’ HIV medical providers will select the antiretroviral regimens to be used. Bias would be introduced if medical providers selected antiretroviral therapy regimens differently based upon knowledge of whether their patient had been randomized to DAART or to SAT. For example, it is possible that medical providers would be more likely to select an antiretroviral therapy regimen that is dosed once daily in individuals enrolled to DAART. This might lead to significant differences between the groups in the use of specific antiretroviral drugs or combinations that could confound the analysis. To avoid this potential source of bias, each medical provider will be asked to specify the particular antiretroviral regimen that he or she will prescribe prior to participant randomization. Our clinical trial is flexibly designed to assess the efficacy of DAART in patients with a range of clinical characteristics, and antiretroviral needs. The study coordinator will contact the data manager for random treatment assignment. Randomization (1:1; performed with Stata, version 8.0, College Station, TX), stratified by prior antiretroviral exposure (naïve or experienced), and study site (PAODD, New Hope, or Day Break), will be performed in blocks randomly varying sized 2 to 6. Antiretroviral naïve will be defined as having less than 4 weeks exposure to antiretroviral drugs.

DAART arm

Site managers will take verbal orders or receive facsimiles of prescriptions from participating medical providers. The site managers will transcribe the medication information to standardized pharmacy order forms, which specify how medications are to be packaged together. We have established a relationship with a single pharmacy, Johns Hopkins Pharmaquip, which will be used for all sites except the VA. Since veterans receive medications free of charge through the VA system, medications for this study will be prepared and packaged at the VA pharmacy. In accordance with pharmacy practice and guidelines, a licensed pharmacist will prepackage all doses of therapy in re-sealable plastic bags. Four-week supplies of therapy will be pre-packaged and will be delivered to the methadone clinics. Pre-packaged therapy will be stored in locked cabinets at each site. Participants will be given a 3-day “emergency supply” of their therapy to permit continued therapy on unplanned absences from the OTP. The site managers will replenish emergency supplies as needed.

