We will carry out a primary unadjusted analysis comparing study endpoints in the DAART and SAT arms. Two-sided P values < 0.05 will be considered to be statistically significant. The primary endpoint for this study will be suppression of the viral load below 50 c/ml evaluated at the 3 follow-up visits during the active intervention period (3, 6 and 12 months). Statistical generalized linear models for repeated observations will be used with the generalized estimating equations (GEE) approach to account for intra-person correlation. An intent-to-treat rule will be used, with missing values excluded. An 18-month follow-up (6 months after DAART intervention concludes) will be performed as a secondary analysis to assess durability. A supplementary on-treatment analysis will also be conducted. Secondary, multivariate analyses will be used to adjust for differences in possible confounding variables that may arise despite randomization. Data collection for the study will include detailed demographic, clinical, and psychosocial factors that may be associated with study outcomes, including prior opportunistic conditions, hepatitis B and C, baseline CD4 count and HIV RNA level, prior treatment experience, and validated metrics of drug and alcohol abuse, depression, and quality of life. We will assess whether adjustment for potential confounders, using multivariate modelling techniques, affects study inferences.For the analysis of immune restoration, we will use an intention-to-treat approach, with last observation carried forward for missing data points. The mean change in CD4+ cell count from baseline will be compared in the study arms at the designated follow-up times. Alternatively, a survival analysis approach will be used with time until first CD4 increase >100 or counts >500 as the outcome and censoring at last visit for each person.

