The development of new antiretroviral drug resistance will be compared in the DAART and SAT arms. Genotypic antiretroviral resistance testing will be performed on the last available plasma sample from (3, 6, 12, or 18 months) when the HIV RNA > 500 c/ml and the subject remains on antiretroviral therapy. Stored plasma from baseline will be run simultaneously to determine if new resistance mutations have developed. Antiretroviral resistance testing is generally not possible at viral loads below 500 c/ml to 1,000 c/ml. Drug resistance mutations will be interpreted according to the classification system of the International AIDS Society – USA [3]. Development of antiretroviral resistance will be defined as the presence of  1 major resistance mutation in the protease or reverse transcriptase genes during study follow-up that was not present at baseline. Subjects with HIV RNA levels < 500 c/ml at all follow-up time points will be considered to have not developed drug resistance. Participants who are lost to follow-up, or who have HIV RNA levels > 500 c/ml, but in whom genotypic antiretroviral resistance testing is not technically feasible, will be omitted from the analysis. Exploratory analyses are planned on treatment-naïve and –experienced subgroups, and on differences in the development of protease inhibitor-, non-nucleoside reverse transcriptase inhibitor-, and nucleoside reverse transcriptase inhibitor-associated resistance mutations.

Retention to opiate agonist therapy will be compared in the DAART and SAT arms using survival analysis techniques. Follow-up time will be modeled from the date participants initiated opiate agonist therapy (origin), with subjects coming under observation at study enrollment, to account for delayed entry and potential lead time bias. Subjects will be considered to have failed when they discontinue or are discharged from methadone maintenance therapy. We will also compare the proportion of participants with active substance abuse at baseline and during the study in the DAART and SAT groups. Active substance abuse will be defined as having a urine toxicology screen positive for drugs of abuse or self-reported (ACASI) illicit drug use, or at-risk alcohol use in the 3 months preceding the survey assessment. Logistic regression with generalized estimating equations, will be used to compare the longitudinal risk of active substance abuse in the study groups, with standard errors adjusted for repeated observations.

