**Statistical power**

In this analysis, we will use methods that can incorporate repeated measurements and account for possible intra-person correlations. Such methods include generalized linear models with generalized estimating equation (GEE) approach or random effects models that can handle binary as well as continuous outcomes. Thus, overall, the number of observations available for comparison of the experimental and control arms of the study will be increased and missing observations will be excluded only for the time points where values of the outcome are missing. Calculations of sample sizes are based on models for longitudinal data analysis (Diggle PJ, Heagerty P, Liang KY, Zeger SL. Analysis of Longitudinal Data. 2002 Oxford University Press, Publ.) are shown in the following table.

The table below shows the power to detect a range of deltas in the DAART arm according to different viral suppression rates in the SAT arm, assuming alpha=0.05, enrollment of 60 per study arm, an intra-subject correlation of 0.2, and 15% loss to follow-up over one year. The table demonstrates >80% to detect deltas >0.20 across varying assumptions.

| **Table. Study Power with sample size of 60 per arm.** | | | | |
| --- | --- | --- | --- | --- |
| **Proportion in control (P0)** | **Delta in DAART arm (P1-P0)** | | | |
|  | **0.15** | **0.18** | **0.20** | **0.25** |
| 0.25 | 0.659 | 0.804 | **0.875** | **0.969** |
| 0.30 | 0.628 | 0.778 | **0.854** | **0.962** |
| 0.35 | 0.609 | 0.762 | **0.842** | **0.958** |
| 0.40 | 0.599 | 0.756 | **0.838** | **0.958** |

|  |  | | |
| --- | --- | --- | --- |
|  |  |  |
|  |  |  |  |
|  |  |  |  |
|  |  |  |  |
|  |  |  |  |
|  |  |  |  |
|  |  |  |  |
|  |  |  |  |
|  |  |  |  |
|  |  |  |  |
|  |  |  |  |

Differences of 15% to 20% in viral suppression rates are frequently considered to be evidence of therapeutic superiority in clinical trials comparing antiretroviral regimens. The detectable difference afforded by our sample size is conservative compared to the differences that we estimated in our pilot study. At 6 months and 12 months the absolute differences in viral suppression between DAART and the methadone maintained group who were self-administering HAART were +30 and +23, respectively.

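### The main GEE for active substance abuse omits the participant's baseline status, which the trial already measures; the comparison stays valid but loses some precision and protection against chance imbalance

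*Protocol*

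**What the plan says.** The statistical plan in the Protocol's Study Statistics section sets a general rule: "We will carry out a primary unadjusted analysis comparing study endpoints in the DAART and SAT arms". It then defines active substance abuse as a composite of a positive urine screen, self-reported illicit drug use or at-risk alcohol use, and gives two analyses. One is descriptive in form: "We will also compare the proportion of participants with active substance abuse at baseline and during the study in the DAART and SAT groups". The other is the model: "Logistic regression with generalized estimating equations, will be used to compare the longitudinal risk of active substance abuse in the study groups". The plan allows for the correlation between a participant's visits when it computes the standard errors. No covariate is named for this model, and no list of visits is given.

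The baseline value is collected. The Study Summary says: "Outcomes data will be obtained at study assessment visits at baseline, 3 months, 6 months, 12 months, and 18 months". The allocation does not balance on it. The enrolment section has: "Randomization (1:1; performed with Stata, version 8.0, College Station, TX), stratified by prior antiretroviral exposure (naïve or experienced), and study site". The design diagram adds HIV RNA as a stratification factor, but no part of the protocol adds substance use.

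Two other places matter. The statistical plan also provides for secondary multivariate analyses to adjust for differences that arise despite randomisation, and lists measures of drug and alcohol abuse among the factors collected. The table of secondary outcomes names a covariate for some outcomes: initial CD4 count in a CD4 model, and prior time in the methadone programme in the model for retention in opioid treatment.

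**The concern.** A participant's drug and alcohol use before randomisation is likely to be among the best predictors of use afterwards, and here it is recorded with the same definition. Leaving it out of the main model has two costs. First, the stable differences between participants that baseline status could explain stay in the error term, so the standard error is larger than it need be. Second, with about 60 per arm and no stratification on this factor, the arms can differ at baseline by chance, and part of that difference carries into the follow-up contrast.

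The protocol does take the baseline value into account for CD4 count. Active substance abuse is in the same position, with a baseline value of the outcome itself, yet its model has no such term.

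**Working it through.** **Inputs from the protocol.** Significance level: "Two-sided P values < 0.05 will be considered to be statistically significant". The power section, written for viral suppression, assumes "enrollment of 60 per study arm, an intra-subject correlation of 0.2, and 15% loss to follow-up over one year". Three follow-up visits (months 3, 6 and 12) are those of the primary endpoint. The Study Summary and the end of the power section still mention 200 participants; I use 60 per arm because the power table does.

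**The plan's own figure.** Effective observations per arm = 60 × 0.85 × 3 / (1 + 2 × 0.2) = 153 / 1.4 = 109.3. A two-sided two-proportion test then gives 0.878 for a control rate of 0.25 and a difference of 0.20, against 0.875 in the table. All 16 cells agree within 0.008. The table is sound, but it concerns viral suppression. The protocol states no power, rate or correlation for active substance abuse.

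**Assumptions for this outcome.** 51 evaluable per arm (60 × 0.85), the same three visits, exchangeable correlation ρ between all visits including baseline, and rates of 60% in SAT and 40% in DAART. The rates and any ρ other than 0.2 are mine; 0.2 is borrowed from viral suppression.

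**Formulas.**
- Variance factor without baseline: (1 + 2ρ)/3.
- Variance factor with baseline as a covariate: (1 + 2ρ)/3 − ρ².
- Variance of the arm difference: [0.6 × 0.4 + 0.4 × 0.6]/51 × factor = 0.00941 × factor.
- Power: Φ(0.20/SE − 1.96).

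**Worked at ρ = 0.2.** The factors are 0.467 and 0.427, a ratio of 0.914. The standard errors are 0.0663 and 0.0634. Power is Φ(1.06) = 85.5% without and Φ(1.20) = 88.4% with the baseline term.

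| ρ | Variance ratio | Variance saved | Power without | Power with | 51 per arm is worth |
|---|---|---|---|---|---|
| 0.2 | 0.914 | 9% | 85.5% | 88.4% | about 56 |
| 0.3 | 0.831 | 17% | 80.6% | 87.2% | about 61 |
| 0.4 | 0.733 | 27% | 75.8% | 87.4% | about 70 |
| 0.5 | 0.625 | 38% | 71.4% | 89.1% | about 82 |

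If month 18 were a fourth outcome visit, the variance ratios would be 0.900 at 0.2, 0.709 at 0.4 and 0.600 at 0.5.

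**Simulation check.** Two simulations of the logistic GEE, 51 per arm and three visits, agree in direction.
- 400 replicates, exchangeable working correlation, effect size set separately in each row: 63% to 66% at a baseline-to-follow-up correlation of 0.19, 56% to 72% at 0.43, and 54% to 79% at 0.59. The Monte Carlo standard error is about 2.5 points.
- 600 replicates, independence working correlation: 88.5% to 90.7% at 0.15, 81.2% to 83.7% at 0.25, and 76.3% to 86.5% at 0.40.

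At 0.25 the simulated gain (2.5 points) is about half of what the formula gives (83.0% to 87.6%, 4.6 points), so the formula may flatter the gain at low correlations.

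**Chance imbalance.** With 60 per arm and an assumed baseline prevalence p, the between-arm difference has standard deviation √(2p(1 − p)/60): 8.4 points at p = 0.3 and 9.1 at p = 0.5. A difference of 10 points or more then arises in 23% to 27% of trials, and of 15 points or more in 7% to 10%. With similar variances at baseline and follow-up, about ρ times the imbalance carries over: a 10-point imbalance shifts the follow-up contrast by about 0.2 × 10 = 2 points at ρ = 0.2, and by 0.5 × 10 = 5 points at ρ = 0.5.

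**The case against.** The strongest reply is that an unadjusted comparison is a legitimate choice in a randomised trial. Its test and confidence interval already allow for chance imbalance, and the covariates of a secondary model are often left to the SAP. The first part stands: nothing here is invalid. The second stands less well, because the protocol does not simply leave the question open. It makes the main comparison unadjusted, and it names covariates for other secondary outcomes.

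Next, the protocol already plans secondary multivariate adjustment, with drug and alcohol measures among the candidates, and will check whether adjustment alters the inferences. This softens the point. But that plan is generic, assigns no covariate to this model, and leaves the main result unadjusted.

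The size is also uncertain. At the only correlation in the document the gain is about 3 power points. Larger gains need a correlation of about 0.3 or more, and baseline may predict month 12 less well than the exchangeable assumption implies. The 60% and 40% rates are illustrative. Drug use is also analysed separately in the secondary-outcome table, as the proportion of screens positive for opiates or cocaine, so this GEE is not the only evidence on substance use. All of this stands and keeps the point small.

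Finally, because the text mentions baseline together with on-study assessments, a reader might infer that baseline enters the GEE as one more outcome row under a single arm term, which would dilute a 20-point difference to 20 × 3/4 = 15 points. A reader might likewise infer a significance test of baseline proportions. The protocol states neither: the baseline comparison and the GEE are in separate sentences, and no test is named for the baseline proportions.

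**Conclusion.** The point holds as a minor, worthwhile improvement to a secondary analysis. The main model for active substance abuse leaves out a baseline measure that is collected under the same definition and is not a stratification factor. The loss is one of efficiency and of robustness to chance imbalance. It should not be read as bias.

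The variance saving is about 9% (about 3 power points) at a correlation of 0.2, and about 27% to 38% at correlations of 0.4 to 0.5. These figures rest on three follow-up visits, 51 evaluable per arm and exchangeable correlation; the power figures also rest on rates of 60% and 40%. The correlation for this outcome is not in the protocol, so the upper end is conditional.

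Nor is the gain entirely free. In a logistic model, adding a covariate changes the odds ratio from a marginal to a conditional one, so the arm effect has to be standardised to keep its meaning.

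**What to change.** In the active-substance-abuse paragraph of the statistical plan:
- State that the outcome rows of the GEE are follow-up visits only, and list them.
- Prespecify baseline active-substance-abuse status (yes/no) as a covariate in the main model.
- Report the arm effect as a standardised (marginal) risk difference or odds ratio, averaging predicted risks over the baseline distribution of all participants.
- Keep the unadjusted GEE as a supporting analysis.

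The cost is a few lines of analysis text. No new data, visits or staff are needed. The small downsides are that participants without a baseline urine or survey result need a stated rule, such as a missing category, and that the standardisation step must be programmed.

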**Statistical power**

In this analysis, we will use methods that can incorporate repeated measurements and account for possible intra-person correlations. Such methods include generalized linear models with generalized estimating equation (GEE) approach or random effects models that can handle binary as well as continuous outcomes. Thus, overall, the number of observations available for comparison of the experimental and control arms of the study will be increased and missing observations will be excluded only for the time points where values of the outcome are missing. Calculations of sample sizes are based on models for longitudinal data analysis (Diggle PJ, Heagerty P, Liang KY, Zeger SL. Analysis of Longitudinal Data. 2002 Oxford University Press, Publ.) are shown in the following table.

The table below shows the power to detect a range of deltas in the DAART arm according to different viral suppression rates in the SAT arm, assuming alpha=0.05, enrollment of 60 per study arm, an intra-subject correlation of 0.2, and 15% loss to follow-up over one year. The table demonstrates >80% to detect deltas >0.20 across varying assumptions.

| **Table. Study Power with sample size of 60 per arm.** | | | | |
| --- | --- | --- | --- | --- |
| **Proportion in control (P0)** | **Delta in DAART arm (P1-P0)** | | | |
|  | **0.15** | **0.18** | **0.20** | **0.25** |
| 0.25 | 0.659 | 0.804 | **0.875** | **0.969** |
| 0.30 | 0.628 | 0.778 | **0.854** | **0.962** |
| 0.35 | 0.609 | 0.762 | **0.842** | **0.958** |
| 0.40 | 0.599 | 0.756 | **0.838** | **0.958** |

|  |  | | |
| --- | --- | --- | --- |
|  |  |  |
|  |  |  |  |
|  |  |  |  |
|  |  |  |  |
|  |  |  |  |
|  |  |  |  |
|  |  |  |  |
|  |  |  |  |
|  |  |  |  |
|  |  |  |  |
|  |  |  |  |

Differences of 15% to 20% in viral suppression rates are frequently considered to be evidence of therapeutic superiority in clinical trials comparing antiretroviral regimens. The detectable difference afforded by our sample size is conservative compared to the differences that we estimated in our pilot study. At 6 months and 12 months the absolute differences in viral suppression between DAART and the methadone maintained group who were self-administering HAART were +30 and +23, respectively.

A second factor to consider is the effect size that would be required to make DAART feasible and cost-effective in clinical practice. A recently published paper by Goldie and coworkers [4] explored the economic aspects of adherence-promoting interventions in HIV-infected individuals treated with ART. The authors calculated costs per quality-adjusted life year (QALY) for hypothetical adherence interventions across a wide range of program costs and effect sizes. Effect size was measured in terms of the reduction in the rate of virological failure that was achieved by an intervention. Based on published data, the authors estimated that time- and labor-intensive adherence interventions, like DAART, would cost approximately $500 per person-month. The analysis indicated that such interventions would need to reduce rates of virologic failure by 25% or more to fall below $50,000 per QALY, the customary benchmark for cost-effectiveness. Our observed virologic failure rate in subjects taking self-administered therapy was 75%; a 25% reduction in this failure rate is 56%; 75% minus 56% is an absolute difference of 19%. Thus the Goldie analysis suggests that relatively expensive and intensive adherence interventions, like the one proposed in our study, would need to demonstrate an absolute increase in the viral suppression rate of 20% or more to be cost-effective in clinical practice. Our study is powered to detect an effect size of this magnitude or larger. Thus, based on both the range of effect sizes estimated from our pilot study and cost-effectiveness considerations we believe that our proposed enrollment of 200 individuals will provide adequate statistical power to address our proposed hypotheses.

1. Early stopping rules.

Not applicable

1. **Human Biological Samples, if collected provide information to address all of the following points:**
2. Will samples from living individuals be studied?

Yes

1. Will new samples be obtained and/or will pre-existing samples be studied?

New Samples

1. Will identifiers or codes be retained that could link the identity of the subject to the sample?

Yes

1. Describe procedures to protect against unauthorized use and loss of confidentiality of the samples or inadvertent release of confidential information.

Each study participant will be assigned a unique identification number. This identification number will be used on each data form and clinical specimen to facilitate linkage of data. Names and other obvious identifiers will not be used on forms or clinical specimens. Data collection forms from our pilot study will be modified to create forms tailored for this randomized controlled trial. Study charts will be stored on-site at the methadone clinics in locked file cabinets. The data manager will enter information from paper forms into the electronic database. A programmer will design a Microsoft Access relational database, which will link data from the various sources by unique identifying number. Computers used for data entry will be password protected and data will be backed-up each night.

Clinical specimens (blood and urine samples) will be obtained by the study coordinator at assessment visits, and, in some cases, for study eligibility screening. In addition to the unique identification number, clinical specimens will be further identified by a two digit visit code, a one digit code for specimen type, and a one digit code identifying the specimen aliquot for banked plasma.

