Inclusion criterion number 4 is designed to assure equal access to therapy at study enrollment. ART will not be provided as part of this study. Coverage for ART will be addressed through patients’ primary care clinics. In our study population, antiretroviral therapy coverage is generally obtained through Medicaid or the Maryland AIDS Drug Assistance Program (MADAP). Our site managers will assist individuals in accessing appropriate resources, but participants will not be enrolled until medication coverage and receipt of prescriptions from a medical provider has been verified. Exclusion criterion 3 is designed to exclude individuals with such extensive drug resistance that viral suppression is unlikely, even with high-level adherence. A summary resistance profile will be compiled that assumes that any resistance mutation or phenotypic drug resistance documented in the past is never lost. The cumulative mutation list will be entered into the Stanford University web-based HIV drug resistance database ([http://hivdb.stanford.edu](http://hivdb.stanford.edu/)) for analysis. Drugs in the proposed regimen will be considered to be fully active (i.e., score=1.0) if categorized as “susceptible” or “potential low-level resistance”, and to be partially active (i.e., score=0.5) if categorized as “low-level resistance” by the Stanford database. Drugs in the proposed regimen with “intermediate“ or “high-level” resistance will not be assumed to have any antiviral activity. Results from phenotypic resistance tests (if available) will be incorporated into the assessment individual drug activity. Enfuvirtide (fusion inhibitor) and raltegravir (integrase inhibitor) will be assumed to be fully active if they have not been used previously. CCR-5 inhibitors (e.g., maraviroc) will be assumed to be fully active if an agent in this drug class has not been used previously and a tropism assay performed within the previous 4 weeks shows exclusively R5-tropic virus. Scores form each drug in the proposed regimen will be summed for a “regimen activity score.” To be eligible for the study a participant’s “regimen activity score” must be greater than or equal to 1.5.

Enrollment and randomization

120 participants will be enrolled to assess the outcomes of this study.

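### The protocol gives two unreconciled enrolment targets, 200 and 120; the only power calculation is for 120, so the closing claim of adequate power for 200 has no calculation behind it

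*Protocol*

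**What the plan says.** Two places in the protocol give a total of 200:

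- Study Summary: "Two hundred participants will be randomly assigned 1:1 self-administered antiretroviral therapy (SAT) or directly administered antiretroviral therapy (DAART".
- Statistical power, closing sentence: "we believe that our proposed enrollment of 200 individuals will provide adequate statistical power to address our proposed hypotheses".

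Three places give 120:

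- Study Design flow diagram: N = 60 in the SAT box and N = 60 in the DAART box.
- Enrollment and randomization: "120 participants will be enrolled to assess the outcomes of this study".
- Statistical power: the table is computed "assuming alpha=0.05, enrollment of 60 per study arm, an intra-subject correlation of 0.2, and 15% loss to follow-up over one year", and its title reads "Study Power with sample size of 60 per arm".

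The power section claims more than 80% power for differences above 20 percentage points. Its cost-effectiveness argument also settles on an absolute gain of 20 points or more as the effect to detect.

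**The concern.** The target sample size tells the sponsor, the sites and the ethics boards when recruitment is complete. As written, a trial that closes at 120 could be called complete or 80 participants short, and a trial that continues to 200 could be called on plan or 80 over (67% more than 120). The last sentence of the sample-size justification also attaches its conclusion to a number that differs from the one used in the table just above it. A reader cannot tell whether the table is out of date or the sentence is.

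Both totals are described as participants enrolled or randomised, so they cannot be read as, say, screened versus randomised. All five places are operative text of the current version; none is part of a change log.

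**Working it through.** **Inputs, all from the protocol**

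- Two-sided 5% level: "Two-sided P values < 0.05 will be considered to be statistically significant" (statistical plan).
- m = 3 measurements per participant, the endpoint being "evaluated at the 3 follow-up visits during the active intervention period (3, 6 and 12 months" (statistical plan).
- Correlation within a participant ρ = 0.2 and 15% loss (Statistical power).
- 1:1 allocation (Enrollment and randomization).
- Control suppression rate P0 from 0.25 to 0.40 (power table).

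The protocol cites a textbook on longitudinal data but prints no formula. I assume the usual two-proportion formula with exchangeable correlation and pooled variance under the null.

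**Formula**

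Variance factor = [1 + (m − 1)ρ]/m = (1 + 2 × 0.2)/3 = 0.4667.

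Effective n per arm, n_e = enrolled per arm × 0.85 / 0.4667:

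- 60 per arm: 51/0.4667 = 109.3
- 100 per arm: 85/0.4667 = 182.1

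Power = Φ{[δ√n_e − 1.96√(2p̄(1 − p̄))] / √(P0(1 − P0) + P1(1 − P1))}, where P1 = P0 + δ and p̄ is the mean of P0 and P1.

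**Reproducing one printed cell (P0 = 0.25, δ = 0.20, 60 per arm)**

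- P1 = 0.45 and p̄ = 0.35.
- δ√n_e = 0.20 × 10.454 = 2.091.
- 1.96√0.455 = 1.322.
- Denominator = √(0.1875 + 0.2475) = 0.660.
- Power = Φ(0.769/0.660) = Φ(1.166) = 0.878. The protocol prints 0.875.

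With 100 per arm, only √n_e changes, to 13.496. Then δ√n_e = 2.699 and power = Φ(1.377/0.660) = Φ(2.088) = 0.982.

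**Both sizes across the control rates**

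| P0 | δ 0.20: printed | 120 enrolled | 200 enrolled | δ 0.15: printed | 120 enrolled | 200 enrolled |
|---|---|---|---|---|---|---|
| 0.25 | 0.875 | 0.878 | 0.982 | 0.659 | 0.660 | 0.867 |
| 0.30 | 0.854 | 0.860 | 0.976 | 0.628 | 0.631 | 0.844 |
| 0.35 | 0.842 | 0.849 | 0.972 | 0.609 | 0.613 | 0.828 |
| 0.40 | 0.838 | 0.846 | 0.971 | 0.599 | 0.604 | 0.820 |

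Over all 16 printed cells (δ of 0.15, 0.18, 0.20 and 0.25), the largest gap between printed and recomputed power at 120 is 0.008. With unpooled variance it is 0.017. Other readings do not fit. At δ = 0.20, 60 per arm without loss gives 0.898 to 0.924, and 100 per arm without loss gives 0.987 to 0.993. The table therefore describes 60 enrolled and 51 evaluable per arm, as its title says.

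**The case against.** The strongest reply is that nothing of substance fails. The only numerical power in the protocol is labelled for 60 per arm, agrees with the flow diagram and the enrolment section, and reproduces for that size. The adequacy conclusion concerns effects of 20 points or more, and the protocol also cites pilot differences of 23 and 30 points. At 20 points power is above 80% with either total. If 200 were the real target, the table would understate power. All of this stands.

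It also rules out two stronger readings that a reader might infer:

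- **That the stated power does not belong to the trial being run.** The documents do not support this. The table belongs to a 120-participant design, which is the better-supported size.
- **That the protocol presents the trial as well powered for 15 points, so that a null result would be over-read.** It makes no such claim. It prints 0.599 to 0.659 at 15 points and claims more than 80% only above 20. It does describe differences of 15% to 20% as frequently taken to show superiority, but that is a remark about a range, not a power claim at its lower end.

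An empty table follows the power table in the text available. Whether it once held content cannot be told. Even a calculation for 200 there would leave the two enrolment targets in conflict.

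The reply does not remove the contradiction in the number to be randomised. A separate analysis plan could not cure it either, because the protocol itself sets both targets.

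**Conclusion.** The point holds as an internal contradiction about the enrolment target, not as an error in the power calculation. The total is 200 in the Study Summary and the closing power sentence, and 120 in the flow diagram, the enrolment section and the power table. The adequacy claim for 200 has no matching calculation in the readable text.

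The choice of total moves power at 20 points from 0.84 to 0.88 (printed, 120) to about 0.97 to 0.98 (200), both above 80%. At 15 points it moves power from 0.60 to 0.66 up to about 0.82 to 0.87, so there the two sizes fall on opposite sides of 80%. The figures for 200 rest on the protocol's own assumptions (ρ = 0.2, 15% loss, three visits, two-sided 5%) and on the formula that reproduces its table.

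A reader might also infer that 200 is a remnant of an earlier plan. That is plausible, since the flow diagram, the enrolment section and the only calculation all agree on 120, but the protocol does not say so. The sponsor has to confirm which total is current. The correction is still necessary, because the number to be randomised must be unambiguous.

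**What to change.** State one total throughout and tie the power conclusion to it.

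- **If the total is 120:** replace 200 with 120 in the Study Summary and in the last sentence of the power section. Word the conclusion as about 84% to 88% power for a 20-point difference with 60 per arm, under the stated assumptions. The 15-point figures are already in the table. The cost is two sentences in an amendment and no change to the design.
- **If the sponsor confirms 200:** change the flow diagram to 100 per arm, correct the enrolment section, and recompute the power table and its stated assumptions for 100 per arm. The cost is a slightly larger amendment, plus recruitment of 80 participants beyond the 120 that those sections now give.
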